# Taking the LEAP: study protocol for a randomized, multicentre, naturalistic, efficacy trial of the compuLsive Exercise Activity theraPy (LEAP) - a cognitive behavioral program specifically targeting compulsive exercise in patients with eating disorders

**DOI:** 10.1186/s12888-021-03356-2

**Published:** 2021-07-23

**Keywords:** Compulsive exercise, Eating disorders, Treatment, Efficacy trial

## Abstract

**Background:**

About half of Swedish eating disorder patients report exercising compulsively and compulsive exercise (CE) is prevalent in all diagnoses and both genders. Yet there are no systematic treatments targeting CE in specialist care. This study aims to evaluate the effects of The CompuLsive Exercise Activity TheraPy (LEAP) - a promising group treatment targeting compulsive exercise, in Swedish eating disorder patients.

**Method:**

One hundred twenty-eight adult females and males suffering from anorexia nervosa, bulimia nervosa or other specified feeding and eating disorders (type 1, 2, or 4) with CE will be recruited via four specialist eating disorder treatment units. Participants will be randomized to receive treatment as usual (control group) or treatment as usual plus LEAP (intervention group). The groups will be assessed on key variables (e.g., BMI, eating disorder symptoms, exercise cognitions and behaviors) at three occasions: initially, after 3 months and after 6 months.

**Discussion:**

The project takes place in a clinical setting, including both male and female patients with different eating disorder diagnoses with CE, enabling a good indication of the efficacy of LEAP. If our results are positive, LEAP has the potential of benefiting about half of the eating disorder population, with remission and recovery hopefully improving as a result.

**Trial registration:**

The trial is registered with the ISRCTN registry (registration date 2020-03-25), trial ID: ISRCTN80711391.

## Background

Compulsive exercise (CE) is a key factor in eating disorder (ED) etiology, development, and maintenance [1, 2]. In adult patients, increased levels of CE are related to more severe psychopathology, increased suicidality, longer hospitalizations, increased relapse risk, and a more chronic course in anorexia nervosa (AN [1, 3–5];). Patients who continue or initiate CE during treatment have 1-year remission rates at roughly half of that among patients without CE or patients who discontinue CE during treatment [3]. In our nationwide study, CE was reported by about half of all ED patients [3]. Previous studies have found CE prevalence to be highest in AN [6], but in our sample patients with bulimia nervosa (BN) and patients with other specified feeding and eating disorders (OSFED) reported the highest prevalence of CE [3]. More importantly, CE was prevalent in all ED diagnoses and almost as common in both genders. Of note, a 2011 nationwide study on Swedish ED patients [7] found lower overall CE rates, but higher rates of binge-eating and purging, than we did. This suggests that CE is becoming more prevalent as a symptom, and/or that there might be gradual symptom-shifting among ED patients over the years.

To date, there is no “gold standard” treatment to tackle CE. However, ours and others’ results indicate a clear need to systematically address CE in ED treatment. The empirically based, targeted programme LEAP [8] aims to educate patients about CE and how it is maintained, challenge maladaptive beliefs and behaviors, and equip patients with strategies promoting healthy exercise. LEAP is founded on the same theoretical principles as the evidence-based ED treatment Cognitive Behavioral Therapy Enhanced (CBT-E [9];) and may be offered as a complement to CBT-E. LEAP is delivered in one initial individual session and eight group sessions. LEAP has been evaluated in two pilot studies and one RCT. In these studies, focusing adult patients with AN, LEAP reduced pathological exercise, ED psychopathology, general psychopathology, and length of hospitalization; it also improved attitudes and beliefs toward exercise (which in turn has proven important for outcome [10];), BMI, and quality of life [11–13]. These findings need to be confirmed at other sites and with other ED diagnostic groups. Of note, the patients in the RCT had suffered from AN (known as an illness notoriously difficult to treat) for an average of 6 years- a considerably long time, yet they made important progress. The effects of LEAP with other ED diagnostic groups and patients with shorter illness duration may therefore be even greater. To our knowledge, there are no existing systematic efforts targeting CE in Swedish specialist care.

## Method

### Objectives, design and setting

#### Objectives

The project aims to evaluate the efficacy of LEAP at reducing pathological exercise and improving ED pathology in Swedish patients diagnosed with AN, BN, or OSFED, in a naturalistic randomized controlled trial (RCT).

##### Primary research question

What are the treatment effects of LEAP on ED diagnosis, ED cognitions, CE behaviors and cognitions, BMI, emotion regulation and general psychopathology, after completion of the LEAP protocol.

##### Secondary research questions

Are there initial factors (e.g., BMI, emotion regulation, compulsivity) that predict a more favorable outcome for patients in the LEAP group? Is LEAP perceived as a feasible and acceptable treatment for patients?

#### Study design

The trial is a naturalistic two-armed parallel open-label superiority randomized efficacy trial, with recruitment from four Swedish specialist ED clinics. Eligible adult patients will be recruited via the clinics and randomized to treatment as usual (TAU) or TAU+LEAP, where LEAP will run in parallel with TAU. Key outcome variables in both arms are measured at initial assessment, after 3 months, and 6 months after initial assessment. Although most TAU+LEAP participants are expected complete the LEAP program prior to T2 assessment, a few may terminate LEAP prior to T3 (see Participant timeline).

#### Setting

The project is a collaboration between Karolinska Institute (KI) and four Swedish specialist ED treatment units: Eriksbergsgården in Örebro, Region Örebro; Ätstörningsenheten in Göteborg; Ätstörningsenheten in Uppsala; and Stockholms Centrum för Ätstörningar in Stockholm. Project management is done at KI while recruitment and the intervention take place at the units. These are medium to large units providing equivalent evidence-based care. The project related processes are equivalent at the units.

##### Therapists

LEAP-therapists are clinicians with vast experience working with patients with eating disorders and some experience of addressing CE in this population. Therapists at study start are licensed psychologists, physiotherapists, and licensed psychotherapists; other medical professions with ED experience could be included later due to potential staff changes. All therapists delivering the LEAP groups have received the same training to maximize adherence. In case of staff changes in LEAP therapists, any new therapist will receive equivalent training. All LEAP session will be audiotaped; two random sessions from each LEAP group will be externally assessed to monitor adherence and fidelity.

### Participants, intervention, and recruitment

#### Eligibility criteria

*Inclusion criteria:* male and female patients, ≥18 years, with AN, BN or OSFED (1. Atypical AN, 2. BN with low frequency and/or limited duration of symptoms, 4. purging disorder/compensatory behaviors after small food amounts), reporting CE at initial assessment (e.g., measured by EDE-Q version 6, item 18, see *Instruments*), and receiving outpatient care at the specialized ED treatment units. As more females than males seek treatment, there will be more females than males in the final sample.

*Exclusion criteria:* inability to communicate in Swedish, psychotic disorder, and/or BMI < 14.

#### Study consent

Subjects are first informed orally by project affiliated unit staff with extensive knowledge on the project, followed by oral or written information from the project manager (also the LEAP principal investigator; PI) or project coordinator (PC). Formal participant information and written study consent are managed and collected through the online data collection and participant management system BASS Core Facility (BASS; see *Data collection and management*) using a governmentally and financially approved secure electronic signature system (Bank-ID; https://www.bankid.com/en). Written participant information in BASS include details about the project, participation, potential risks and benefits of participation, usage of participant data, how to find study results, insurance and remuneration, and the voluntary basis of participation. Contact details to the PI, the KI Data Protection Officer and the Swedish Data Protection Authority are also provided. Patients consent to project participation, to medical records being collected and to have their data collected as described. There are no ancillary studies; all collected data are related to this project.

#### Interventions

The intervention group receive LEAP in addition to standard outpatient care (TAU) running in parallel, while the control group receive only TAU. Standard outpatient care includes a medical contact, psychoeducation about EDs, in most cases a CBT-based treatment via a personal therapeutic contact and/or group therapy, and meal-support. Everyone has a personalized treatment plan. There are no systematic interventions focusing on pathological exercise in TAU, which means that TAU+LEAP will clearly deviate from standard care.

##### Choice of comparators (choice of control interventions)

These patients receive standard outpatient care (i.e., TAU). TAU was chosen as comparator due to the naturalistic study design; TAU with varying content is what patients displaying CE usually receive within specialized ED treatment settings.

##### LEAP

LEAP is a semi-structured, problem-oriented group CBT, with psychoeducation specifically focusing on physical activity, behavioral experiments, and cognitive activities. The overarching aim for LEAP is to promote “healthy” exercise. Specific aims are to educate patients about the maintenance of CE, promote insight into factors affecting beliefs and behaviors toward exercise, introduce skills to help challenge maladaptive beliefs and behaviors, introduce adaptive emotion coping strategies, and prevent relapse. Each group contains 4–8 participants. The program consists of 1 individual session (Session 0) and 8 one-hour group sessions over four consecutive weeks. Sessions are preceded by homework tasks. Groups will be held at the treatment units. Two therapists at each treatment unit and three additional therapists from the research group (two acting as supervisors) have been trained in LEAP by the project coordinators and [name] (CM) and clinical psychologist [name] (TC).

##### The Swedish LEAP manual (Table 1)

Since the publication of the original manual [8], several modifications have been made in both research and clinical settings (e.g., individual treatment, addition of individual session 0, reordering of sessions). The Swedish LEAP manual has reordered the sessions and included the individual session 0 held prior to the LEAP group. The Swedish manual has also, in consultation with the originator CM, replaced the session on physical movement at a low weight in AN (“Activity AN”) with a session focusing perfectionism and self-compassion as this was considered more suitable for the target group (i.e., outpatients with mixed EDs). See Table 1 for a session overview of the Swedish LEAP manual.

**Table 1 Tab1:** LEAP session overview

Session	Name	Content
Session 0	Individual LEAP Exercise Profile	Initial information and introduction of the CBT-model of the maintenance of compulsive exercise. Completion of the LEAP Exercise Profile and individual maintenance formulation.
Session 1	Orientation	Group introduction, presentation of central concepts, the CBT-model, and the Exercise Profiles. Introduction of the behavioral experiment, self-monitoring task, and homework.
Session 2	Healthy and Unhealthy Exercise	Review differences between healthy and unhealthy exercise behaviors and attitudes. Connect to the CBT-model and Exercise Profiles. Introduction of the cognitive restructuring technique.
Session 3	Myths and Facts	Highlight the difference between myths and facts, and how myths (false beliefs, assumptions) can maintain unhealthy attitudes and behaviors toward exercise.
Session 4	Compulsive Exercise and Eating Disorders	Presentation of the relationship between compulsive exercise and eating disorders, and their respective maintaining factors. Introduction of the problem solving and guided discovery techniques.
Session 5	Psychological Dependence on Mood Regulation and ‘Exercise Addiction’	Highlight the role of exercise in regulation mood and emotions, and the risk of psychological dependence (‘addicion’) to exercise. Introduction of alternative strategies to manage emotions.
Session 6	Behavioural Rigidity	Explore how strict rules and unrealistic standards results in rigid, compulsive behaviors, both in relation to exercise and other life areas. Introduction of the cost analysis technique.
Session 7	Perfectionism and Exercise	Highlight the relationship between perfectionism, self-criticism and compulsive exercise. Introduction of acceptance and self-compassion as alternative approaches towards performance.
Session 8	Initiating and Maintaining Factors	Explore differences in reasons for starting and continuing to exercise. Summarizing the LEAP intervention, techniques, remaining challenges and relapse prevention.

##### Modifications and discontinuation

LEAP will not be modified for individual participants. There are no formal criteria for intervention discontinuation; LEAP-therapists discuss potential adverse events for individual participants (e.g., severe psychiatric deterioration) with the PI who then formally decides on possible intervention discontinuation. No additional assessments are required in case of treatment discontinuation or study withdrawal.

#### Adherence

The LEAP intervention begins with an individual session where the intervention is individually conceptualized, assumed to increase personal relevance and motivation. All group sessions begin with an opportunity to raise questions and homework is always followed up. Participants are continually reminded of the importance of actively participating in the session and the importance of completing homework tasks, self-monitoring and behavioral experiments. Potential obstacles are examined to improve adherence.

#### Concomitant care

All patients receive individually personalized TAU. CE will not receive systematic attention since this is not standard practice. However, the attention given to exercise as a symptom may vary between therapists. Thus, to control for potential deviations from standard practice in this regard, both study and control participants will answer questions about treatment content at the last assessment point, that is, questions about the content of their treatment including how much attention has been given to pathological exercise, if so, in which ways. Additionally, LEAP therapists are encouraged not to have LEAP participants (neither controls nor study) in individual treatment. However, due to smaller unit size for three of four units, there might be violations to this guideline. If so, LEAP therapists are instructed to have equal numbers of intervention and control patients in individual treatment.

#### Provisions for post-trial care

Most participants are expected to remain within their TAU after project participation, however, no ancillary or post-trial care is expected due to project participation. All participants are covered by the KI insurance and a patient injury insurance (‘Patientskadeförsäkring’), covering compensation for those suffering potential harm from trial participation.

#### Participant timeline (Fig. 1)

Participants come to the clinic via clinical or self-referral. Within the first three visits, they are assessed using standardized diagnostic interviews, clinical rating scales, and self-report questionnaires. Eligible patients will be asked if they are interested in study participation by clinicians on participating units. Those who are interested will be contacted and formally recruited by the project manager or assistant. They are provided a link to BASS for study consent and the first assessment battery which can be completed directly. Afterwards, they are allocated to either control or intervention group. All participants continue TAU independent of group allocation; for those in the intervention group, LEAP starts when there are enough allocated patients (> 4 patients). After consent, study timeline is at minimum 182 days (three assessment points 90 days apart). Most participants in the intervention group will complete the LEAP program prior to T2 assessment, but due to variation in patient influx at units, some may instead terminate LEAP prior to T3. Participants are no longer included in the study after completed 6-month assessment (T3).

**Fig. 1 Fig1:**
[figure not shown]
LEAP participant timeline

#### Sample size

Based on pilot data and power analysis with beta = .80, alpha = .05, effect size f = .25 and an estimated correlation between pre- and post-measures of .50, a total of 98 patients are required: 49 patients receiving LEAP and 49 controls. With an estimated drop-out rate of 30%, we will enroll 128 participants (64/arm). As there is a minimum of 4 participants in a LEAP group, length of time between initial assessment and first session of LEAP will vary for patients. This variation will need to be considered a covariate.

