### Data collection and management

#### Outcomes

*Primary outcomes:* remission of ED diagnosis, improved ED psychopathology, and reduced pathological exercise behaviors and cognitions.

*Secondary outcomes:* normalized weight (BMI) and reduced general psychopathology.

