#### Instruments/measures

##### Primary outcomes

Structured Eating Disorder Interview (SEDI [14];) is a semi-structured interview assessing ED diagnostic criteria according to DSM-IV. It is performed at T3; remission status (i.e., ED left or not) is used as outcome (binary data). The SEDI is also performed at three units at initial assessment to determine initial diagnosis. The SEDI has adequate psychometric properties [14]. The Eating Disorder Examination Questionnaire (EDE-Q [15];) is a 28-item questionnaire scored 0–6 (no days-all days) measuring severity of self-reported ED pathology the past 28 days. It generates an overall Global Scale and the subscales Restraint, Eating Concerns, Weight Concerns and Shape Concern. It also measures prevalence of ED behaviors such as restriction, binge-eating, purging and CE. This study will use information of presence and frequency of CE (binary and count data) and ED psychopathology scales as outcomes (continuous data). The EDE-Q has satisfactory psychometric properties [9, 16].The Compulsive Exercise Test (CET [17]; is a 24-item questionnaire scored 0–5 (never true-always true) measuring core psychological, behavioral, and emotional aspects of CE. It generates five subscales: Avoidance and rule-driven behavior, Weight control exercise, Mood improvement, Lack of exercise enjoyment, and Exercise rigidity. The LEAP treatment targets the aspects measured by the CET and all subscales are used as outcomes (continuous data). The CET has satisfactory psychometric properties [1, 17, 18].

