### Statistical methods

#### Outcomes (methods for analyzing primary and secondary outcomes)

To evaluate the LEAP treatment effect (primary objective) the data will be analysed per protocol and based on intention to treat. The first analysis will include all controls (TAU) and participants that complete the program (LEAP+TAU) and answer the questionnaires. The T3 assessment point will be used for post treatment data unless the participants completed the program before T2. Each continuous outcome measure will be used as a response variable in a linear regression model with group allocation and baseline value as predictors. Logistic regression will be used for categorical outcomes. Additional covariates in the models will include gender, clinic, and time between T1 and first treatment session. Since the removal of drop out and noncompliant subjects in the per protocol analysis may lead to overestimation of the treatment effect, we will also perform the same analysis on the basic of intention to treat. Here all subjects who were randomized to LEAP and answered the questionnaires will be included in the treatment group, independently whether they participated in the LEAP sessions. Assessment points with at least CET and EDE-Q will be included in analyses in relation to the primary outcome. If data is missing on CET and/or EDE-Q, the timepoint will not be considered for analysis. There will be no item level missing data (technically prohibited in BASS). The percentage of patients withdrawing from the program despite the initial intention to participate will be considered as a feasibility marker. To compare proportions of dropout and loss to follow-up within the groups, conventional two-sample Z-tests will be used. To identify prognostic factors associated with a good response to LEAP (secondary objective), the treatment group will be subjected to additional analysis where the outcome of interest is used as response variable in linear or logistic regression model and potential prognostic factors (e.g., BMI, type of ED) are used as predictors. These analyses will include all participants with complete data for each specific model.

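### The 98-patient, power-.80 statement rests on a continuous-outcome calculation but is not limited to the continuous outcomes, so its power is not established for the binary primary outcomes (remission, presence of CE)

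*Protocol article*

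**What the plan says.** The Sample size section gives one calculation for the whole trial: "power analysis with beta = .80, alpha = .05", then "effect size f = .25 and an estimated correlation between pre- and post-measures of .50, a total of 98 patients are required", split as 49 per arm. Enrolment is then set at 128 (64 per arm) for an expected drop-out of 30%. The section does not say which outcome the calculation serves.

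The Outcomes section lists the primary outcomes as "remission of ED diagnosis, improved ED psychopathology, and reduced pathological exercise behaviors and cognitions". Under Instruments/measures, the SEDI entry says "It is performed at T3; remission status (i.e., ED left or not) is used as outcome (binary data", and the EDE-Q entry uses presence of CE as binary data and its frequency as a count, next to the continuous EDE-Q scales. The CET subscales are continuous.

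Under Statistical methods, continuous outcomes go into a linear regression with group and baseline value. For the others, "Logistic regression will be used for categorical outcomes".

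The Eligibility criteria require an eating-disorder diagnosis (AN, BN or OSFED) and CE reported at initial assessment. No remission rate, CE rate, odds ratio or risk difference is given for either arm.

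**The concern.** Cohen's f and a pre-post correlation describe a continuous measure taken twice. The correlation matters to the answer: it brings the required total down from 128 to 98. A binary outcome that has the same value for nearly every patient at entry offers nothing for that correlation to act on. Yet remission, the first-listed primary outcome, and presence of CE stand under the same unqualified statement of 98 patients and power .80.

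What is at stake is how a null result would be read. The Discussion presents improved remission as part of LEAP's potential and links national implementation to beneficial effects in this trial. A reader who meets a non-significant remission result could set it against a power of 80% that was not calculated for that outcome.

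**Working it through.** **Inputs from the Sample size section.** alpha = .05 (sidedness not stated; two-sided assumed, which reproduces the total); power .80 (printed as beta); f = .25, which for two equal groups is d = 2f = 0.50; r = .50; 49 per arm.

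**1. Reproducing 98.** Noncentral F with 1 and N - 2 degrees of freedom.
- Repeated-measures ANOVA, between-groups effect, m = 2 measurements: lambda = f²·N·m / (1 + (m - 1)r) = 0.0625 × 2N / 1.5 = 0.0833N.
- Linear regression on baseline (ANCOVA): lambda = f²·N / (1 - r²) = 0.0625N / 0.75 = 0.0833N.

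The two are numerically identical. Power is 79.9% at N = 96 and 80.8% at N = 98, so 98 is the smallest even total. Because the ANCOVA form matches the planned regression, the calculation suits the continuous outcomes.

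**2. What the correlation contributes.** Without it, lambda = 0.0625N. The required total is then 128, and N = 98 gives 68.8%. That this 128 equals planned enrolment is a coincidence: enrolment is 98 × 1.30 = 127.4, rounded up to an even number.

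**3. Whether it can apply to the binary outcomes.** At entry every patient has an eating disorder and reports CE. Remission status and presence of CE are therefore constant, or nearly so, at baseline. A constant has no correlation with a later value and removes no variance.

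**4. Size, under assumptions the documents do not supply.** Two proportions, pooled-variance normal approximation, two-sided .05, 49 per arm. The value d = 0.5 is carried over in three ways, with assumed control rates of 20%, 30%, 40% and 50%. For presence of CE, take absence of CE as the event.

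| Conversion of d = 0.5 | 20% | 30% | 40% | 50% |
|---|---|---|---|---|
| Arcsine, h = .5 | 69% | 69% | 69% | 69% |
| Log-odds, OR = exp(.5π/√3) = 2.48 | 51% | 58% | 60% | 58% |
| Probit shift of .5 | 45% | 49% | 50% | 49% |

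The direct formula for h gives Φ(.5√(49/2) - 1.96) = 70%. The overall range is about 45-70%.

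Sensitivity at 49 per arm:
- A control rate of 10% gives about 35% power on the log-odds and probit scales.
- A larger effect, 30% versus 60%, gives 86%.

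**5. Detectable difference at 80% power.** This needs an assumed control rate but no conversion of d.

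| Evaluable per arm | 20% | 30% | 40% | 50% |
|---|---|---|---|---|
| 49 | 26 points | 28 points | 28 points | 27 points |
| 44.8 (64 × 0.70) | 28 points | 29 points | 29 points | 28 points |

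**6. Evaluable number.** 128 × 0.70 = 89.6, about 90 in total. At that number even the continuous calculation gives about 77%, not 80%.

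**The case against.** The strongest reply is that the section never claims 80% power for remission. Its terms plainly describe a continuous measure, and sizing a trial on one type of outcome is ordinary practice. A condensed article may also leave power for further primary outcomes to the full protocol or SAP. This stands in part: the arithmetic is right, it agrees with the planned baseline-adjusted regression, and nothing here faults the calculation for the CET and EDE-Q scales. It does not remove the scope problem. The statement is the only one in the article, it names no outcome, and it says this many patients are required for a trial whose first-listed primary outcome is binary.

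A second reply is that power for the binary outcomes is undefined, not shown to be low. That also stands. A reader might infer from the unsuitable formula that remission is powered at 45-70%, or that an effect of the planned size would be missed in 30-55% of trials. The documents support neither. No effect was planned for remission, and nothing in them equates d = 0.5 on a questionnaire with any particular odds ratio for a diagnosis. The only remission information, in the Background, is that 1-year remission is roughly halved when CE continues or begins during treatment. That is a ratio without absolute rates and is not a LEAP effect.

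Third, eligibility mentions the EDE-Q item only as an example of how CE may be established, so a few patients might lack CE on that item at entry. Baseline variation is therefore best described as essentially absent. The frequency of CE, as a count, can still gain from baseline adjustment and is outside this point.

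**Conclusion.** The point holds as a matter of scope. The total of 98 and the power of .80 are correct for a continuous outcome with d = 0.5 and r = .50, and they are not established for SEDI remission or presence of CE. This follows from the eligibility criteria, the outcome definitions and the sample-size inputs, without any assumed rate. The size of the shortfall is conditional: about 45-70% power at 49 per arm if d = 0.5 is carried over to proportions and control rates are 20-50%, with values near 35% or above 80% under other assumptions.

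The tempting converse, that the continuous outcomes are secure at 80%, is not supported either. It is true at 98 evaluable, but 128 enrolled less the stated 30% leaves about 90.

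The statement should be corrected; nothing in the design has to change.

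**What to change.** In the Sample size section:

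- State that the calculation and its power apply to the continuous primary outcomes (CET and EDE-Q scales) under baseline-adjusted regression. Add that 128 less 30% leaves about 90 evaluable, with about 77% power, so that 80% is not reaffirmed without that qualification.
- For remission and presence of CE, state assumed control rates and give the detectable difference at the evaluable number: about 26-28 percentage points at 49 per arm and about 28-29 at roughly 45 per arm, for control rates of 20-50%.
- Add one sentence that a non-significant remission result will be reported as an estimate with its confidence interval and not as evidence of no effect.

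The cost is a rewritten paragraph and a less favourable stated power for the binary primary outcomes. This point calls for no extra patients and no change to procedures.

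### The 30% drop-out allowance was added to 98 instead of divided out, so 128 enrolled leaves about 90 evaluable patients and about 77% power

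*Protocol article*

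**What the plan says.** The Sample size section gives the planning inputs as "power analysis with beta = .80, alpha = .05, effect size f = .25" together with "an estimated correlation between pre- and post-measures of .50". From these it concludes that "a total of 98 patients are required: 49 patients receiving LEAP and 49 controls". It then allows for attrition: "With an estimated drop-out rate of 30%, we will enroll 128 participants (64/arm"). The Method part of the Abstract repeats the total of 128.

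The statistical methods section plans, for each continuous outcome, a "linear regression model with group allocation and baseline value as predictors". The per-protocol analysis takes all controls together with the LEAP participants who complete the programme and answer the questionnaires. For intention to treat, "all subjects who were randomized to LEAP and answered the questionnaires will be included in the treatment group", whether or not they attended sessions. A timepoint without CET or EDE-Q data is left out of the analysis. The article describes no imputation.

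**The concern.** A drop-out rate is the share of enrolled patients who are lost, so the evaluable number is the enrolled number times (1 − rate). To end with 98 after losing 30%, one divides 98 by 0.7. The article's 128 is what results from adding 30% to 98, which undershoots. The stated requirement, the stated drop-out rate and the stated enrolment cannot then all be true.

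At stake is whether the trial meets its own 80% power criterion under its own attrition assumption. Because only patients who answered the questionnaires enter the models, patients lost to assessment come off the analysed number.

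**Working it through.** **Inputs, all from the Sample size section.** Power 0.80 (printed as beta, which must mean power); alpha 0.05 (sidedness not stated; a two-sided test is assumed because it reproduces the article's figure and a one-sided test gives 76); f = 0.25, equivalent to a standardised difference of 0.50 with two equal groups; pre-post correlation ρ = 0.50; 98 required; drop-out 30%; 128 enrolled.

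**Step 1: reproduce 98.** For the planned baseline-adjusted regression, the F test for group has noncentrality λ = f²N / (1 − ρ²), with 1 and N − 3 degrees of freedom.

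- N = 96: λ = 0.0625 × 96 / 0.75 = 8.00, power 0.799.
- N = 98: λ = 0.0625 × 98 / 0.75 = 8.17, power 0.808.

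The smallest even total that reaches 80% is 98, so the article's requirement reproduces exactly. A repeated-measures between-group test with two measurements, λ = f²N × 2 / (1 + ρ) on 1 and N − 2 degrees of freedom, gives the same λ at ρ = 0.50 and the same answer. The fault therefore lies in the inflation step alone.

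**Step 2: the inflation.**

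| Calculation | Total | Per arm |
|---|---|---|
| 98 × 1.3 | 127.4, rounded up to 128 | 64 |
| 98 / 0.7 | 140 | 70 |

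The article's figure matches the first row. It is 12 patients below the second.

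**Step 3: what 128 delivers at 30% drop-out.**

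- Evaluable: 128 × 0.7 = 89.6, about 90, or 45 per arm. That is 8 fewer than 98.
- Power at N = 90: λ = 0.0625 × 90 / 0.75 = 7.50, power 0.773. At N = 89 it is 0.768.
- Break-even drop-out: 1 − 98/128 = 0.234, or 23.4%.
- If each patient drops out independently with probability 0.30, the chance of keeping at least 98 of 128 is about 6%.

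**Step 4: what 140 would deliver.** 140 × 0.7 = 98 evaluable, 49 per arm, power 0.808.

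**The case against.** The arithmetic slip is hard to contest. The case on the other side is about what follows from it.

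*Drop-out is not defined.* The statistical methods section uses the word largely for leaving the programme and names loss to follow-up separately. A LEAP patient who stops attending but still answers the questionnaires stays in the intention-to-treat set. The per-protocol set keeps the controls and removes LEAP non-completers. If the 30% fell only on the LEAP arm, about 45 would be compared with 64, and power would be about 0.84, above the target. This is a fair reason to attach a condition to the 77%: it assumes 30% of outcome data lost in both arms. It does not rescue the text. The Sample size section applies one overall rate and raises both arms from 49 to 64, and even on this reading the LEAP arm would end with about 45, not 49.

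*The gap is small against the uncertainty of the inputs.* At 45 per arm, a pre-post correlation of 0.55 gives power 0.802 and one of 0.40 gives 0.725. That is true, and it limits the practical weight of the point. It does not make the stated figures consistent.

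*128 could be a different calculation.* It is also the total for an unadjusted post-treatment comparison at a standardised difference of 0.5. The article does not present it that way; it gives 98 as the requirement and ties 128 to the drop-out rate.

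**Conclusion.** The point holds: the sample-size statement is wrong as written. Under the article's own 30% drop-out, 128 enrolled gives about 90 evaluable patients instead of 98, and power of about 77% against a target of 80% (80.8% at 98). Enrolment is 12 short of the 140 that the stated rate requires, and 128 suffices only for drop-out up to 23.4%.

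The power figure rests on a two-sided test at 5%, f = 0.25, ρ = 0.50, and equal loss of outcome data in the two arms. The shortfall is modest, 2.7 points below the target. It concerns the stated power and does not affect the type I error rate or the treatment-effect estimate.

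**What to change.** Correct the sentence in the Sample size section in one of three ways:

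- **Keep 128 and the 30% rate, and restate the power.** For example: with 128 enrolled and 30% drop-out, about 90 patients (45 per arm) are expected to be evaluable, giving about 77% power for f = 0.25; at least 80% power requires drop-out of no more than about 23%.
- **Keep 128 and 80% power, and restate the allowance** as about 23%, if that rate can be justified.
- **Keep the 30% rate and 80% power, and enrol 140** (70 per arm), changing the Abstract to match.

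Whichever is chosen, record 140 as the number that 30% drop-out would need, and say whether drop-out means loss of outcome data or leaving LEAP.

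The first two options cost one sentence and a less favourable stated power or attrition margin. The third costs 12 more patients, 6 per arm, in a trial whose Discussion already names inclusion pace as a main concern. The Trial status section says recruitment had not begun, so when the article was written the figure could be put right before any patient was enrolled.
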